**Fig. 1 Fig1:**
[figure not shown]
Consolidated Standards of Reporting Trials (CONSORT) flow diagram for the ERUTECC study. ERUTECC is a randomised, stepped-wedged trial within the EFFECTS study. EFFECTS has initiated 35 centres, of which 32 are active. We will exclude the five top recruiting centres because we believe they have reached their full potential, and the planned intervention is too weak

### Study type

We will use a randomised, stepped-wedge cluster design, where every step provides data before and after intervention, but not at the same point in time.

Figure 2 illustrates the stepped-wedge cluster study in our study. As the name indicates, the intervention has 11 different steps, and the schema takes the form of a wedge. Figure 3 is a schematic diagram of the time schedule of enrolment, interventions (including any run-ins and washouts) and assessments for the participating centre.

**Fig. 2 Fig2:**
[figure not shown]
The randomised, stepped-wedge cluster design for the ERUTECC study. In ERUTECC, we use a stepped-wedge cluster design. First the centre is classified as low or medium recruiting. Second, the centres are randomised in each class ensuring that at least one low and one medium recruiting centre is included in every step. Each centre has a 60-day running-in period (yellow), followed by a 60-day post-intervention period (blue). The intervention (teleconference) is done after the 60-day running-in period, and every step provides data before and after intervention, but not at the same point in time. We will add up all patients for all 11 steps in the 60-day running-in period and compare this with the inclusion rate for all centres’ 60-day post randomisation period

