### Rationales for the study

Currently, the EFFECTS trial includes 30 patients per month [11], and recruitment projections would take the trial beyond its current funding. Thus, a new strategy is needed.

After talking to the principal investigators (PIs) at the centres, and to trialists in the UK with similar studies, we are confident that five of the top recruiters (Danderyd Hospital, Karolinska University Hospital Solna, Sundsvall Hospital, Mora General Hospital and Skaraborg Hospital Skövde) have reached their full potential, and little would be gained from the planned intervention.

We have asked the centres via a survey, and have also discussed this in person at investigator meetings, what they consider to be the most important barrier to recruitment for trials. They have said that the most important barrier is the lack of time for the physician responsible to identify the right patients and to carry out the study-specific procedures at baseline. The second most important factor is the lack of time for all other study personnel. They have a high clinical workload at their clinic and do not have any time specifically dedicated to working with clinical trials. It is the head of department (verksamhetschef) who is responsible for finances and personnel. Without the support of the head of department there will hardly be any change in recruitment. We will, therefore, invite the head of department (verksamhetschef) at the local centre to the teleconference in addition to the PI and the research nurse. Hopefully, we can work together to identify what could be done to provide more opportunities at the clinic to do research for both physicians and nurses within working hours. We have chosen a teleconference because it is time effective and less expensive than a face-to-face meeting. In addition, we hypothesised that a commitment contract would make it more personal for the local centre.

We have followed the 2013 SPIRIT (Standard Protocol Items: Recommendations for Interventional Trials) Checklist [12] in conjugation with the 2013 SPIRIT explanation and elaboration guidance for protocols of clinical trials [13] (Additional file 1).

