### The rationale for the trial design

We have chosen the stepped-wedge cluster randomised study design [14] for three reasons. First, it is not possible for us to carry out the intervention at 14–15 centres at the same time. Second, we believe that all medium and low recruiting centres could gain from the intervention, and in a stepped-wedge cluster design all centres are exposed. Every step provides before and after observations, and every step switches from control to become exposed to the intervention. Third, we have noticed a seasonal variation in recruitment. During the Christmas and Easter holidays, and especially during the summer, recruitment is falling. This intervention gives a realistic view of recruitment throughout the whole year. To the best of our knowledge, only one randomised stepped-wedge study in the field of stroke has been done [15].

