**Fig. 3 Fig3:**
[figure not shown]
The flow of participants in the ERUTECC study. In ERUTECC, each centre follows the same flow, with a 60-day period of running in, and a 60-day post-intervention period (teleconference). The figure shows one step. We will add up all patients for all 11 steps in the 60-day running-in period and compare this with the inclusion rate for all centres’ 60-day post randomisation period

In ERUTECC, all centres have a 60-day running-in period and a 60-day post-intervention period. Our plan is to start in September 2017 and finish in October 2018.

The 27 sites will be divided into two categories: medium and low recruiters. The rationale for this is that we do not want to risk all medium recruiters falling into the same step, for example the summer period, which usually a low-recruiting period. The centre will be randomised in terms of the order in which intervention will be performed, leading to (at least) one medium and (at least) one low recruiter in each of the 11 steps (Fig. 2).

All centres in the EFFECTS study, their classification, type and numbers of patients are listed in Table 1.

**Table 1 Tab1:** Centres in EFFECTS as of 31 August 2017

Centre	Type of centre	Number of stroke patients per year^a^	First included patient in EFFECTS (yyyy-mm-dd)	Total number of patients recruited	Percentage of number of patients recruited^b^
01 Danderyd Hospital	SU at hosp	837	11/11/2014	110	14%
02 Karolinska University Hospital Solna	SU at univ hosp	542	10/20/2014	98	12%
03 Skaraborg Hospital Skövde	SU at hosp	422	10/20/2014	56	7%
04 Hässleholm Hospital	SU at hosp	203	3/23/2015	32	4%
05 Uppsala University Hospital	SU at univ hosp	496	4/20/2015	39	5%
06 Karolinska University Hospital Huddinge	SU at univ hosp	488	4/8/2015	15	2%
07 Mora General Hospital	SU at hosp	226	4/15/2015	49	6%
08 Falu General Hospital	SU at hosp	510	5/13/2015	12	1%
09 Lidköping	SU at hosp	162	10/6/2015	12	1%
10 Capio St Göran’s	SU at hosp	697	6/24/2015	51	6%
11 Visby General Hospital	SU at hosp	132	11/4/2015	7	1%
12 Norrland University Hospital	SU at univ hosp	355	9/22/2015	12	1%
13 Kristianstad Central Hospital	SU at hosp	334	9/24/2015	11	1%
14 Norrtälje Hospital	SU at hosp	165	12/9/2015	1	0%
15 Helsingborg General Hospital	SU at hosp	391	11/18/2015	15	2%
16 Skåne University Hospital Malmö	SU at univ hosp	478	12/18/2015	16	2%
17 Halland Hospital Halmstad	SU at hosp	374	12/1/2015	36	4%
18 Mälar Hospital Eskilstuna	SU at hosp	246	2015-22-23	10	1%

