### Statistical methods

We will compare the numbers of included individuals 60 days before the teleconference with the numbers of subjects 60 days post intervention. The null hypothesis is that there will be no difference before and after. We consider a 20% increase in recruitment rate as clinical relevant, although it is arbitrarily chosen.

Statistical example:Sixty days pre-teleconference: 60 individualsSixty days post-teleconference: 78 individualsThat is, 78/60 = 1.3; a 30% increase in recruitment

In EFFECTS, we have a screening list in which we note all eligible individuals who have been considered as candidates for EFFECTS. If these patients are not part of the study, the reason is noted. Usually the reasons are administrative and non-willingness. We will compare the numbers of randomised patients with the eligible patients on the screening list.

The outcome of the study is the number of included patients per centre. Inclusion is available through our electronic randomisation system, and we will keep a separate log for every teleconference. If a centre refuses to be part of ERUTECC, we will still include the centre in the analysis (intention-to-treat). In addition, we will also do a ‘per-protocol analysis’.

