## Trial status

The main study – EFFECTS – included its first patient on 20 October 2014, and as of 31 October 2017, 881 patients have been included. The last patient is estimated to be recruited in March 2019, with the last follow-up 1 year later. The ERUTECC will start in November 2017 (Fig. 2) and continue for 1 year.

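### The primary analysis is a pooled before-after ratio that makes no use of the randomised order, so any steady recruitment trend is counted as intervention effect

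*Protocol article*

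**What the plan says.** The protocol article calls ERUTECC a randomised stepped-wedge cluster trial. Centres are classed as low or medium recruiters, and the order of intervention is randomised within each class (Study type; Statistics).

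The analysis is stated several times, always in the same form:

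- Fig. 2 legend: "We will add up all patients for all 11 steps in the 60-day running-in period and compare this with the inclusion rate" of the post period. The Fig. 3 legend repeats it: "compare this with the inclusion rate for all centres’ 60-day post randomisation period".
- The section on statistical methods agrees: "We will compare the numbers of included individuals 60 days before the teleconference with the numbers of subjects 60 days post intervention". Next comes the null: "The null hypothesis is that there will be no difference before and after". The worked example divides one total by another.
- Primary objective and Hypothesis: both are framed as the 60 days after against the 60 days before.

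The target is also given there: "We consider a 20% increase in recruitment rate as clinical relevant". Among the reasons for the design the authors write: "Third, we have noticed a seasonal variation in recruitment". The only planned look at bias over time is an exploratory comparison under Secondary objectives, which sets post-teleconference recruitment against a fixed September-October 2017 baseline.

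**The concern.** In a stepped wedge, calendar time and exposure are confounded within each centre, because exposure always comes later. The randomised order is what allows them to be separated: in a given month, centres already exposed can be compared with centres still waiting. The stated analysis makes no such comparison. It adds up every pre-window, adds up every post-window, and compares the sums.

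Anything that shifts recruitment generally over two months then enters the estimate, whether or not the teleconference did anything. A rise looks like benefit and a fall hides it. Randomising the order does not help, because in every step the post-window is later than the pre-window by the same interval. Balancing medium and low recruiters across steps does not help either; it puts no time control into the estimate.

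What is at stake is attribution. The protocol pays for a randomised order that could support a causal reading, and then fixes an estimator that cannot.

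**Working it through.** **The plan's own figure.** The worked example has 60 patients before and 78 after: 78/60 = 1.30. It reproduces, and it confirms that the estimator is a crude ratio of totals with no time term.

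**Layout of the windows.** The section explaining the stepped-wedge design starts step 1 in September 2017 and step 2 a month later. With month 1 = September 2017, step k (k = 1 to 11) has pre-months k and k+1 and post-months k+2 and k+3. Step 11 then ends in month 14, October 2018, as planned under Study type.

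**Trend.** Suppose the teleconference has no effect and recruitment changes by a factor (1+g) each month. For step k:

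ratio = [(1+g)^(k+2) + (1+g)^(k+3)] / [(1+g)^k + (1+g)^(k+1)] = (1+g)^2

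This does not depend on k, so the pooled ratio is also (1+g)^2, whatever the order. The values of g are assumptions.

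| Trend per month | Pooled ratio, no effect |
|---|---|
| +1% | 1.02 |
| +3% | 1.06 |
| +5% | 1.10 |
| -3% | 0.94 |
| -5% | 0.90 |

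To produce the whole 20% target, g would have to be sqrt(1.20) - 1 = 9.5% per month.

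**Season.** Counting how often each month is a post-month minus how often it is a pre-month, with steps of equal size, gives:

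- Sep 2017 -1, Oct 2017 -2, Nov 2017 -1
- Dec 2017 to Jul 2018: 0
- Aug 2018 +1, Sep 2018 +2, Oct 2018 +1

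For a pattern that repeats each year, the remainder is Aug + Sep - Oct - Nov. Three assumed patterns of summer and Christmas dips gave pooled ratios of 0.98 to 1.00. Regular season is therefore not the problem; drift from one autumn to the next is.

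**Concurrent controls exist.** From November 2017 to August 2018 every month contains both exposed and not-yet-exposed centres.

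**Precision of an adjusted analysis.** Inputs: the Table 1 totals of the 27 centres (407 patients) as relative rates, an assumed 15 patients per month over these centres, an assumed split of 13 medium and 14 low recruiters, and Poisson counts. For the unadjusted windows the expected total is 15 × 2 = 30 on each side, so SE(log ratio) = sqrt(1/30 + 1/30) = 0.26. The other values come from the Poisson information matrix with centre effects.

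| Analysis | SE of log rate ratio |
|---|---|
| 60-day windows, unadjusted | 0.26 |
| 60-day windows, month effects | about 0.6 |
| All centre-months, month effects, single exposure effect | 0.25 |
| All centre-months, month effects, effect by phase since teleconference | 0.27 |

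If centre-month counts are overdispersed (variance μ + 0.3μ², assumed), the last two become about 0.28 and 0.30.

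**The case against.** The strongest reply is that the protocol shows no trend and that sampling noise is larger than the bias. Both parts stand. At 3% per month the bias on the log scale is ln 1.06 = 0.06, about a quarter of the standard error of 0.26. The 20% target is itself only ln 1.2 / 0.26 = 0.7 standard errors, and the adjusted model would not make it easier to detect. The protocol's projection of the last patient in March 2019 implies (1500 - 881)/17 = 36 patients per month, essentially flat.

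A reader might infer a trend from the host trial's counts. The abstract gives 810 patients at the end of August 2017; Trial status says "as of 31 October 2017, 881 patients have been included". That is 71 in two months, against 60 at the stated rate ("Currently, the EFFECTS trial includes 30 patients per month"), a ratio of 1.18. This does not establish drift. Even with 30 per month taken as exact, the 95% interval is 0.92 to 1.49. The count includes the five top recruiters excluded from ERUTECC, it follows the summer low, and those two months are step 1's pre-window, where a rise lifts the baseline.

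A reader might also infer that the error bars would be too narrow because variation between centres is ignored. Statistical methods names no test or interval, so there is nothing to call too narrow.

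The fixed-baseline comparison under Secondary objectives deserves credit as a sign that bias over time was considered. It is exploratory and itself before-after, so it cannot separate trend from effect.

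**Conclusion.** The point holds. The objective, the hypothesis, both figure legends and the statistical methods fix a pooled before-after ratio. It uses neither the randomised order nor concurrent controls, and it is biased by (1+g)^2 under a steady trend in either direction: about 6% at 3% per month and 10% at 5%. This is not detail left to an analysis plan, because the article states the estimator itself.

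The algebra rests only on monthly steps and adjacent 60-day windows. The trend sizes are assumptions, and neither their sign nor their size can be read from the protocol. It would go too far to say that any result would be uninterpretable: a bias of 6-10% under assumed trends is moderate beside the sampling error. The narrower conclusion is that a change in the ratio cannot be attributed to the teleconference by design, although the randomised order would allow it at almost no cost in precision.

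**What to change.** Make the primary analysis a regression of inclusion counts by centre and calendar month:

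- all 27 centres, for the whole of September 2017 to October 2018;
- centre effects and calendar-month effects;
- a log(days) offset, with months split at the teleconference date;
- an exposure term that isolates days 0-60 from later follow-up, so that the target remains the 60-day effect;
- a variance that allows for overdispersion, or a p-value from re-randomising the order within the low and medium strata.

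Report the days 0-60 rate ratio with its 95% interval, and keep the pooled 60/60-day ratio as description. Do not merely add month effects to the 60-day windows, since that raises the standard error to about 0.6. Month effects remove only time changes shared by the centres, and the text should say so.

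The cost is revised analysis wording and a slightly longer program. Inclusions are already in the electronic randomisation system and teleconferences in the planned log, so no new data are needed.

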**Fig. 3 Fig3:**
[figure not shown]
The flow of participants in the ERUTECC study. In ERUTECC, each centre follows the same flow, with a 60-day period of running in, and a 60-day post-intervention period (teleconference). The figure shows one step. We will add up all patients for all 11 steps in the 60-day running-in period and compare this with the inclusion rate for all centres’ 60-day post randomisation period

In ERUTECC, all centres have a 60-day running-in period and a 60-day post-intervention period. Our plan is to start in September 2017 and finish in October 2018.

The 27 sites will be divided into two categories: medium and low recruiters. The rationale for this is that we do not want to risk all medium recruiters falling into the same step, for example the summer period, which usually a low-recruiting period. The centre will be randomised in terms of the order in which intervention will be performed, leading to (at least) one medium and (at least) one low recruiter in each of the 11 steps (Fig. 2).

All centres in the EFFECTS study, their classification, type and numbers of patients are listed in Table 1.

**Table 1 Tab1:** Centres in EFFECTS as of 31 August 2017

Centre	Type of centre	Number of stroke patients per year^a^	First included patient in EFFECTS (yyyy-mm-dd)	Total number of patients recruited	Percentage of number of patients recruited^b^
01 Danderyd Hospital	SU at hosp	837	11/11/2014	110	14%
02 Karolinska University Hospital Solna	SU at univ hosp	542	10/20/2014	98	12%
03 Skaraborg Hospital Skövde	SU at hosp	422	10/20/2014	56	7%
04 Hässleholm Hospital	SU at hosp	203	3/23/2015	32	4%
05 Uppsala University Hospital	SU at univ hosp	496	4/20/2015	39	5%
06 Karolinska University Hospital Huddinge	SU at univ hosp	488	4/8/2015	15	2%
07 Mora General Hospital	SU at hosp	226	4/15/2015	49	6%
08 Falu General Hospital	SU at hosp	510	5/13/2015	12	1%
09 Lidköping	SU at hosp	162	10/6/2015	12	1%
10 Capio St Göran’s	SU at hosp	697	6/24/2015	51	6%
11 Visby General Hospital	SU at hosp	132	11/4/2015	7	1%
12 Norrland University Hospital	SU at univ hosp	355	9/22/2015	12	1%
13 Kristianstad Central Hospital	SU at hosp	334	9/24/2015	11	1%
14 Norrtälje Hospital	SU at hosp	165	12/9/2015	1	0%
15 Helsingborg General Hospital	SU at hosp	391	11/18/2015	15	2%
16 Skåne University Hospital Malmö	SU at univ hosp	478	12/18/2015	16	2%
17 Halland Hospital Halmstad	SU at hosp	374	12/1/2015	36	4%
18 Mälar Hospital Eskilstuna	SU at hosp	246	2015-22-23	10	1%
19 Rehab Station Stockholm	Neuro RH	^c^	11/24/2015	4	0%
20 Skåne University Hospital Lund	SU at univ hosp	634	2/29/2016	9	1%
21 Sundsvall Hospital	SU at hosp	486	12/18/2015	66	8%
22 Sahlgrenska University Hospital	SU at univ hosp	789	4/15/2015	16	2%
23 Högsbo Rehabilitation Hospital	Neuro RH	^c^	3/4/2016	2	0%
24 Stora Sköndal Neurological Rehabilitation Clinic	Neuro RH	^c^	1/22/2016	13	2%
25 Östersund Hospital	SU at hosp	339	3/10/2016	21	3%
26 Alingsås General Hospital	SU at hosp	223	2/25/2016	34	4%
27 Ängelholm Hospital	SU at hosp	232	3/15/2016	16	2%
28 Stockholm Nursing Home	Neuro RH	^c^	4/4/2016	13	2%
29 Örebro Rehabilitation Clinic	Neuro RUH	^c^	10/10/2016	10	1%
30 Norra Älvsborg County Hospital Trollhättan	SU at hosp	699	12/3/2016	4	0%
31 Bromma Geriatric Clinic	Ger RH	^c^	11/24/2016	1	0%
32 Västmanland Hospital Västerås	SU at hosp	411	1/18/2017	9	1%
33 Dalen Hospital	Ger RH	^c^	5/22/2017	2	0%
34 Lindesberg General Hospital	SU at hosp	117	6/15/2017	2	0%
35 Hudiksvall Hospital	SU at hosp	187	4/12/2017	6	1%
Total				810	100%

The centres are numbered in the order they were initiated. Closed centre denotes that the centre is closed for EFFECTS and not included for ERUTECC. *Abbreviations: SU at hosp* Stroke unit at hospital, *SU at univ hosp* Stroke unit at university hospital, *Neuro RH* Neurological rehabilitation hospital, *Neuro RHU* Neurological university hospital, *Ger RH* Geriatric rehabilitation hospital

^a^Numbers of patients in the stroke unit according to the National Swedish Quality Register [19]

^b^Number of patients included divided by total number of stroke patients during active participating time the EFFECTS study as of 31 August 2017

^c^Rehabilitation hospitals/units. The exact number of stroke is not part of the Riksstroke statistics

### Inclusion criteria

Active centre in the EFFECTS study. We will invite all the study personnel at each centre. Study personnel are defined as all persons listed at the delegation list at the time for the invitation. For the meeting to happen, at least the PI, one research nurse and the head of department at the centre/hospital/unit must attend the meeting (*n* = 3).

### Exclusion criteria

Top recruiting centre in the EFFECTS study, i.e. Danderyd Hospital, Karolinska University Hospital Solna, Sundsvall Hospital, Mora General Hospital or Skaraborg Hospital Skövde.

### Preparation before the intervention

This is what we will do before the intervention (teleconference):One person, i.e. the trial manager, trial manager assistant or a PhD student, will contact the local PI or the research nurse approximately 2–3 weeks before a planned meeting and suggest three possible dates for a 1-h meeting. We will schedule the meeting via email or using a DoodleA document is signed in which the PI consents to participate in this intervention study. In this document, the PI also gives a relevant mobile phone number that we can use to get in touch and send text messagesOne week before the meeting, an email with the agenda and PowerPoint presentation attached will be sent to all participantsOne day before, a text message and an email will be sent to all participants as a reminder of the meeting

### The intervention – a structured teleconference

This is a teleconference between the chief investigator (CI) plus the trial manager and the study personnel. The meeting requires that at least the PI, one research nurse and the head of department (verksamhetschef) must attend the meeting. If they are not all able to attend, the meeting will be rescheduled. Ideally, as many members as possible listed on the delegation list will attend the meeting.

The agenda(a) Opening of the meeting (1 min,). Chair: trial manager. Secretary: chief investigator. Keeping track of the time: chief investigator(b) Presentation of all at the meeting (2 min, all)(c) Presentation of EFFECTS, PowerPoint (4 min, chief investigator)The rationale of the study (one slide)An update of overall recruitment (one slide)What we need to do – our aim (one slide)An update of recruitment at the local site (one slide)Discussion of local barriers (5–7 min, all)What can we do at our local centre? (5–7 min, all)Discussion with the head of department about barriers and what can be done (5 min, all)Where do we go from here? Formulate a commitment contract, minimum one item, maximum three items (5–7 min, trial manager)Closing and summary of the meeting (2 min, trial manager)

